### Secondary outcomes

The following secondary outcomes will be assessed using self-report. Each instrument will be administered at T0, T1 and T2, except for the *Net Promoter Score (NPS)* and the items regarding negative effects of the programme.
Cancer-related fatigue using the *Brief Fatigue Inventory (BFI-9)* [62, 63]Cancer-related emotional stress using the standardized *Impact of Event Scale-Revised (IES-R)* [64]Depression using the standardized 9-item *Patient Health Questionnaire (PHQ-9 )* [65, 66]Anxiety using the standardized questionnaire *Generalized Anxiety Disorder 7 item (GAD-7)* [67, 68]Fear of progression using the standardized *PA-F12* (Progredienzangstfragebogen [Fear of Progression]) questionnaire [69, 70]Insomnia using the standardized *Insomnia Severity Index (ISI)* [71]Subjective usefulness of the programme using the *NPS* [72] and several items to assess negative effects of the programme.

Additionally, participants will be asked about specific illness-related parameters including recurrence of breast cancer (local relapse or remote metastasis), frequency of common cold or virus flu, frequency of unscheduled medical encounters, body mass index and the parallel use of psychotherapy at T0, T1 and T2. Furthermore, participants will be asked for open feedback on the programme 15 days after access has been granted.

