**Methods:**

This randomized controlled trial (RCT) will include 360 female breast cancer survivors who have completed the active tumour eradication phase. Participants will be recruited from various settings, including web-based advertisements and Internet forums in German-speaking countries. The main inclusion criteria are a breast cancer diagnosis less than 5 years ago and completion of acute treatment at least 1 month ago, as verified by discharge letter from an oncology treatment centre. Participants will be randomly assigned to either (1) a control group, in which they receive care as usual (CAU) and are given access to *Optimune* after a delay of 3 months (CAU/wait list control), or (2) a treatment group that may also use CAU and will receive 12-month access to *Optimune* immediately after randomization. The three primary endpoints are quality of life, physical activity and diet quality, assessed with the World Health Organization Quality of Life Questionnaire, the International Physical Activity Questionnaire and the Food Quality Questionnaire, at 3 months post-baseline; secondary outcomes include cancer-related fatigue, emotional stress, depression, anxiety, fear of progression, insomnia, usefulness of the programme and negative treatment effects. Online assessments are conducted at baseline (T0), 3 months (T1) and 6 months (T2).

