Given the potential utility of effective digital interventions, our team has developed a novel Internet-based intervention termed *Optimune*. This individually tailored Internet intervention targets female breast cancer survivors and was developed by Gaia, a German research-focused small-to-medium enterprise (SME) with more than 10 years of experience in the development of similar interventions. For example, 12 RCTs have demonstrated the efficacy of *Deprexis*, an Internet intervention for depression developed by the same team with the same technology [32–43]. A recent meta-analysis yielded an effect size of *g* = 0.54 for *Deprexis* [44]. Other evidence-based interventions developed by this group target anxiety disorders, fatigue in multiple sclerosis and harmful drinking as well as depression and anxiety in epilepsy [34, 45–47]. *Optimune* aims to reduce distress, depression, anxiety and, in particular, chronic inflammation in breast cancer survivors (see the Methods/design section for the intervention description).

The goal of this pragmatic RCT [48] is to test the effectiveness of this novel Internet intervention on improvements in quality of life and relevant lifestyle parameters (dietary and exercise habits) among breast cancer survivors over a period of 3 months, in comparison to a control group that only receives access to the intervention after 3 months. Both groups are free to utilize other treatments that may be required; thus, *Optimune* will be offered adjunctively to care as usual (CAU). Because control group participants can access *Optimune* after 3 months, they are on a wait list (WL) only with respect to the Internet intervention. Thus, the control group is best characterized as CAU/WL. It is hypothesized that, at 3 months post-baseline, participants randomized to the intervention group will report higher levels of quality of life, physical activity and diet quality compared to participants randomized to the CAU/WL control condition. In order to examine stability of intervention effects over time, data will also be collected at 6 months. Additional analyses will examine a broad range of secondary outcomes, including cancer-related fatigue, stress, depression, anxiety, fear of cancer progression and insomnia. The subjective usefulness of the intervention will also be examined. Exploratory analyses will be conducted to examine potential negative intervention effects.

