## Methods/design

### Study design

In this parallel-group RCT, participants will be randomized to two groups: (1) a control group, in which they may engage with any treatment and receive access to the Internet intervention after a delay of 3 months (CAU/WL), or (2) a treatment group that immediately receives access to the Internet intervention and may also use CAU (see Fig. 1). The trial aims to maximize external validity by examining the effect of adding a self-management intervention to the realities of current clinical care; it does not aim to maximize internal validity by selecting a maximally homogeneous patient group that does not reflect the clinical reality outside of trials [49]. Participants will be recruited consecutively from various sources, with every woman having an equal chance of being assigned to the intervention or control group (no block randomization). Given the pragmatic design, participants are not blinded to group assignment. Randomization will be performed by the Principal Investigator (PI), using a computer-generated sequence to generate the allocation sequence. However, the PI will not have any access to any participant data prior to performing the randomization. The other researchers who do have access to participant data in order to clarify inclusion/exclusion criteria will not have access to the randomization sequence. Thus, concealed allocation will be ensured.

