**Table 1 Tab1:**
[figure not shown]
Study interventions, measures and measurement points

*WHOQOL-BREF* World Health Organization Quality of Life Questionnaire, *IPAQ* International Physical Activity Questionnaire, *FQQ* Food Quality Questionnaire, *BFI-9* Brief Fatigue Inventory, *IES-R* Impact of Event Scale-Revised, *PHQ-9* Patient Health Questionnaire, 9 items, *GAD-7* Generalized Anxiety Disorder 7-item questionnaire, *PAF-12* Fear of Progression Questionnaire, *ISI* Insomnia Severity Index

^a^Only for intervention group

^b^For each group: 15 days after access was granted

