### Sample size calculation and analysis

To estimate the target sample size, an a priori power analysis was performed with g*power (Version 3.1.9.2) [73]. In order to detect a small to medium effect (*d* = 0.35), a total sample size of 346 participants will be required to achieve a power of 0.80 with an adjusted alpha level of 0.0167 (Bonferroni adjustment because of the three primary endpoints; 0.05/3). An effect of *d* = 0.35 has been shown in previous reviews on psychosocial outcomes in patients with cancer [74–76]. Therefore, we aim to enrol 180 participants per group (total target *N* = 360). Because missing data will be replaced by multiple imputation, the target sample size is not adjusted for anticipated attrition.

In line with recommendations of the CONSORT eHealth statement, we will conduct both intention-to-treat (ITT) and per-protocol (PP) analyses using appropriate statistical procedures such as analysis of covariance (ANCOVA) for primary and secondary outcome measures [51, 77]. Missing data will be imputed for ITT and PP analyses at the primary endpoints after 3 months with multiple imputation (100 imputations, 50 iterations) based on sociodemographic data and available outcomes, following current methodological recommendations [78]. ITT analyses will include data from all randomized participants, with missing data replaced by multiple imputation. For PP analyses, in line with previous studies [40, 45], we will include data from control group participants plus data from intervention group participants who have used the intervention for at least 60 min on at least four separate occasions (i.e. four sessions). For PP analyses, missing data will also be replaced using multiple imputation, in line with recommendations [79]. Bonferroni-adjusted ANCOVAs will be conducted for each primary outcome to test for between-group effects after 3 months using baseline measures as covariates, as recommended for trials with pre- and post-measurement [80].

The reasons that lead to the exclusion of participants will be reported and analysed for patterns [81], that is, systematic differences in their occurrence between the control group and intervention group.

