## Discussion

The present study aims to make a contribution to the literature on Internet interventions for breast cancer survivors, and to test the effectiveness of a potential new treatment option that may help improve the quality of care for this group. There is a need for innovative interventions in this area, given that depression and fatigue are exceedingly common in women after the acute treatment phase, and psycho-oncological treatment provision is often insufficient, particularly in rural areas. To our knowledge, *Optimune* is the first Internet intervention for breast cancer survivors that uses an extensive tailoring approach to convey CBT content to users. It has been specifically designed to address the needs of breast cancer survivors and uses a responsive web-design approach to maximize personal relevance and ensure easy usability.

An advantage of this trial is that diagnoses will be verified by a clinician, which is rare in studies of Internet interventions. Additional methodological strengths include follow-up assessments and the inclusion of an array of validated measures for the primary and secondary outcomes. Of note, potential negative treatment effects will also be assessed, which is rarely done but required to establish the safety of novel Internet interventions. Another strength is that participants will be asked to provide open feedback about the programme.

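### The one outcome labelled as negative effects has no control comparator at 3 months, and the two-arm data that could provide one are not designated as harm outcomes

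*Protocol article*

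**What the plan says.** All references are to the protocol article.

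- **Abstract, Methods.** The secondary outcomes end with "usefulness of the programme and negative treatment effects".
- **Secondary outcomes.** The measure is "several items to assess negative effects of the programme". The other secondary instruments are given at T0, T1 and T2, "except for the *Net Promoter Score (NPS)* and the items regarding negative effects of the programme". The same section schedules recurrence, colds and flu, unscheduled medical encounters, body mass index and psychotherapy use at all three time points, with no restriction by arm.
- **Primary outcomes.** WHOQOL-BREF is assessed as change from baseline at 90 days in both groups.
- **Study design.** Controls get the programme only after 3 months.
- **Background.** "Exploratory analyses will be conducted to examine potential negative intervention effects".
- **Sample size calculation and analysis.** ITT and per-protocol analyses will use suitable procedures, with "analysis of covariance (ANCOVA) for primary and secondary outcome measures" given as an example. The sentence on baseline covariates concerns the primary outcomes.
- **Discussion.** Listed among the strengths: "potential negative treatment effects will also be assessed, which is rarely done but required to establish the safety of novel Internet interventions".

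**The concern.** A report of negative effects attributed to the programme can come only from someone who has used it. Before T1 that means the intervention arm alone. After T1 both arms have access, so the unexposed comparator is gone. The outcome that carries the harm label therefore has no randomised contrast in the one period when the design could supply it.

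This matters in both directions. Distress, fatigue and fear of progression can worsen in breast cancer survivors without any programme, so a user may blame the programme for background worsening. A user may equally get worse because of the programme and not attribute it. A one-arm report cannot tell these cases apart.

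The two-arm data at T1 could answer the question, but the article presents them only as efficacy outcomes or illness descriptors. A comparison of mean scores is a weak screen for harm, because an average benefit can coexist with a minority who deteriorate.

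**Working it through.** **1. Is there a contrast for the designated items?** The items ask about effects of the programme (Secondary outcomes), and controls have no programme until 3 months (Study design). At T1 unexposed controls cannot meaningfully answer them. This follows from those two sections and does not need the body of Table 1, which is not shown.

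**2. What is available in both arms at T1?** BFI-9, IES-R, PHQ-9, GAD-7, PA-F12, ISI, WHOQOL-BREF, recurrence, infections and unscheduled medical encounters. None is described as a harm outcome.

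**3. Can a mean difference hide harm?** Take the design effect of d = 0.35. As an illustration, assume the programme worsens 10% of users by 0.5 SD. The other 90% then need a benefit of x, where 0.9x − 0.1 × 0.5 = 0.35, so x = 0.40/0.9 = 0.44 SD. The mean difference is exactly the effect the trial is designed to find, and one user in ten has been harmed.

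**4. Size of the background.** Assume 10% worsen regardless of arm: 0.10 × 180 = 18 users. The programme items offer no control figure to set against them.

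**5. Precision of a between-arm comparison.** The article gives no figure for harm, so only its sample size can be reproduced. For d = 0.35, two-sided alpha 0.0167 and power 0.80, the t-test calculation gives a total of 344.57, which rounds up to 173 per group, or the stated 346. The target is 180 per group.

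For a risk difference with a common event rate p and n per arm, the 95% half-width is 1.96 × √(2p(1 − p)/n). For p = 0.10 and n = 180 this is 1.96 × √(0.18/180) = 1.96 × 0.0316 = 0.062. The rates and the 25% attrition (180 × 0.75 = 135) are assumptions.

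| Assumed rate | 180 per arm | 135 per arm |
|---|---|---|
| 5% | ±4.5 points | ±5.2 points |
| 10% | ±6.2 points | ±7.2 points |
| 15% | ±7.4 points | ±8.5 points |

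Power at 180 per arm, two-sided alpha 0.05, no attrition:

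| Control vs intervention rate | Power |
|---|---|
| 5% vs 10% | 0.44 |
| 5% vs 15% | 0.89 |
| 10% vs 15% | 0.30 |
| 10% vs 20% | 0.76 |

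The comparison can show a large excess of harm but is imprecise for a small one.

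**The case against.** The strongest reply is that the trial does collect harm-relevant data in both arms. Six symptom scales, recurrence and unscheduled medical encounters are scheduled at T1 without restriction by arm, and ITT analyses of secondary outcomes are planned. This stands. A reader might infer that the trial has no randomised comparison of harm at all, and the documents do not support that. The gap is one of designation and of how the scales are analysed.

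A reader might also infer that the plan commits to a baseline-adjusted ANCOVA that cannot be run on the programme items. It does not. ANCOVA is an example of a procedure for secondary outcomes, and baseline covariates are specified for the primary outcomes.

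The Background calls the analysis of negative effects exploratory and does not confine it to the programme items. The Discussion says such assessment is needed to establish safety, not that these items will prove it. Both points stand and limit the concern.

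The footnote "Only for intervention group" in Table 1 cannot be tied to these items, because the table body is not shown. Nothing here rests on it.

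Last, worsening thresholds and tables are often left to an analysis plan, which is not shown, so their absence from the article is not itself the point. What remains is that the article does name a measure of negative effects, and an analysis plan cannot give that measure a comparator at T1.

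**Conclusion.** The point holds in a limited form. The only outcome designated as negative effects is programme-specific and cannot be compared between randomised arms at T1. The data that could be compared are not designated as harm outcomes, so the strength claimed in the Discussion goes further than the designated measure supports.

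The primary endpoints, the sample size and the rule for trial success are untouched. The practical size is the uncertainty in any safety statement. Programme reports alone give no estimate of excess harm. The data already collected would give one to within about ±4.5 to ±7.4 points with 180 per arm, or ±5.2 to ±8.5 points with 135. These figures rest on assumed event rates of 5% to 15% and an assumed attrition of 25%, none of which the article states. That unexposed controls cannot usefully answer items about the programme is an inference from the wording and the wait-list design, and a secure one.

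**What to change.** Within the exploratory analysis of negative effects announced in the Background, designate these between-arm ITT comparisons at T1:

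- **Worsening.** For PHQ-9, GAD-7, IES-R, PA-F12 and WHOQOL-BREF, the proportion in each arm that worsens from T0 by more than a threshold fixed before any comparison of groups (for example 0.5 baseline SD). Report the risk difference with a 95% CI.
- **Illness events.** Recurrence as a risk difference, with an interval method suited to sparse events, and unscheduled medical encounters as a rate contrast, each with a 95% CI.

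Report the programme items as a descriptive, uncontrolled summary of user reports. Reword the Discussion so that any safety statement reflects the between-arm results and their width.

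The cost is a short addition to the analysis plan and one extra table from data already scheduled in both arms. According to Trial status, recruitment is complete and follow-up is still running, so the thresholds should be fixed before group data are compared. The downside is a few more exploratory comparisons with wide intervals, and probably a more modest safety statement.

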### Sample size calculation and analysis

To estimate the target sample size, an a priori power analysis was performed with g*power (Version 3.1.9.2) [73]. In order to detect a small to medium effect (*d* = 0.35), a total sample size of 346 participants will be required to achieve a power of 0.80 with an adjusted alpha level of 0.0167 (Bonferroni adjustment because of the three primary endpoints; 0.05/3). An effect of *d* = 0.35 has been shown in previous reviews on psychosocial outcomes in patients with cancer [74–76]. Therefore, we aim to enrol 180 participants per group (total target *N* = 360). Because missing data will be replaced by multiple imputation, the target sample size is not adjusted for anticipated attrition.

In line with recommendations of the CONSORT eHealth statement, we will conduct both intention-to-treat (ITT) and per-protocol (PP) analyses using appropriate statistical procedures such as analysis of covariance (ANCOVA) for primary and secondary outcome measures [51, 77]. Missing data will be imputed for ITT and PP analyses at the primary endpoints after 3 months with multiple imputation (100 imputations, 50 iterations) based on sociodemographic data and available outcomes, following current methodological recommendations [78]. ITT analyses will include data from all randomized participants, with missing data replaced by multiple imputation. For PP analyses, in line with previous studies [40, 45], we will include data from control group participants plus data from intervention group participants who have used the intervention for at least 60 min on at least four separate occasions (i.e. four sessions). For PP analyses, missing data will also be replaced using multiple imputation, in line with recommendations [79]. Bonferroni-adjusted ANCOVAs will be conducted for each primary outcome to test for between-group effects after 3 months using baseline measures as covariates, as recommended for trials with pre- and post-measurement [80].

The reasons that lead to the exclusion of participants will be reported and analysed for patterns [81], that is, systematic differences in their occurrence between the control group and intervention group.

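### The stated basis for multiple imputation does not include randomised arm; applied as written, it would attenuate the effect on all three primary endpoints by up to about the missing fraction

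*Protocol article*

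**What the plan says.** Everything relevant is in the protocol article, Sample size calculation and analysis.

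- **Imputation basis:** missing values at the 3-month endpoint are imputed "with multiple imputation (100 imputations, 50 iterations) based on sociodemographic data and available outcomes". The sentence adds that this follows current methodological guidance, with a citation.
- **Where the imputed data go:** "ITT analyses will include data from all randomized participants, with missing data replaced by multiple imputation". The per-protocol set is treated likewise: "For PP analyses, missing data will also be replaced using multiple imputation, in line with recommendations".
- **Analysis model:** "Bonferroni-adjusted ANCOVAs will be conducted for each primary outcome to test for between-group effects after 3 months using baseline measures as covariates".
- **Sample size:** "In order to detect a small to medium effect (*d* = 0.35), a total sample size of 346 participants will be required"; the design power is 0.80 at a Bonferroni-corrected alpha of 0.0167. On enrolment, the article states: "we aim to enrol 180 participants per group (total target *N* = 360").
- **Attrition:** "Because missing data will be replaced by multiple imputation, the target sample size is not adjusted for anticipated attrition". No expected attrition rate is given.

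The sections Secondary outcomes and Study design add two facts that matter here. The questionnaires are repeated at baseline (T0), 3 months (T1) and 6 months (T2). The control group gets the programme after 3 months, so its T2 values follow access.

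**The concern.** An imputation model should contain every variable in the analysis model that it serves. Here the analysis model estimates an arm effect, and the two kinds of predictor named for imputation are background characteristics and outcome data. Arm is neither.

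Without arm, a woman with a missing T1 value gets a draw from a regression fitted to both arms together. Given the same covariates, an intervention participant and a control then have the same expected imputed value. In effect, the imputed part of the sample is assigned no treatment difference beyond what the covariates carry, and the overall estimate is diluted.

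The same imputation serves all three primary endpoints, so every route to the trial's success criterion (an effect on at least one of them) would be affected. There is also little reserve: the sample was not enlarged for drop-out, precisely because imputation was expected to deal with it.

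**Working it through.** **Inputs from the article:** d = 0.35; alpha 0.0167 (0.05/3); power 0.80; stated total 346; target 180 per arm; ANCOVA with baseline as covariate.

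**Assumptions (not in the article):** 10 to 40% missing at T1; correlation 0.5 between baseline and T1; values missing completely at random.

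**1. The plan's own sample size.** Normal approximation, two-sided: n per arm = 2(z₁ + z₂)²/d² = 2(2.393 + 0.842)²/0.35² = 20.93/0.1225 ≈ 171, or 342 in total. With the exact noncentral t distribution, power is 0.7992 at 172 per arm and 0.8019 at 173 per arm. So 2 × 173 = 346 reproduces exactly. At 180 per arm with complete data, power is 0.82.

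**2. Attenuation by formula, when only baseline data predict the missing value.** Let m₁ and m₀ be the fractions missing in the intervention and control arms, and let p₁ = (1 − m₁)/(2 − m₁ − m₀) be the intervention share of the observed values. Without arm, imputed values in both arms centre on p₁d, taking the control mean as 0.

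- Intervention mean: (1 − m₁)d + m₁p₁d
- Control mean: m₀p₁d
- Difference: d[1 − m₁ + p₁(m₁ − m₀)], which is d(1 − m) when missingness is equal

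Equal missingness of 10, 20, 30 and 40% gives 0.315, 0.280, 0.245 and 0.210.

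Unequal missingness:

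- 30% v 10%: p₁ = 0.7/1.6 = 0.4375; factor 0.7 + 0.4375 × 0.2 = 0.7875; effect 0.276
- 40% v 20%: p₁ = 0.6/1.4 = 0.4286; factor 0.6 + 0.4286 × 0.2 = 0.686; effect 0.240

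**3. Simulation of the same setting.** 1,000 trials per row, 180 per arm, normal-model multiple imputation with 20 imputations (the plan has 100), ANCOVA pooled by Rubin's rules, alpha 0.0167.

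| Missing | Estimate, arm included | Estimate, arm omitted | Power, arm included | Power, arm omitted |
|---|---|---|---|---|
| 10% | 0.353 | 0.318 | 0.89 | 0.84 |
| 20% | 0.349 | 0.279 | 0.83 | 0.68 |
| 30% | 0.350 | 0.244 | 0.78 | 0.42 |

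The estimates agree with the formula. Power with arm included can exceed the 0.82 of step 1 because the assumed baseline correlation lowers the residual SD to √(1 − 0.5²) = 0.866. The fall from 0.89 to 0.78 down the column with arm included is the ordinary cost of lost data. Only the gap within a row is due to omitting arm: 0.15 at 20% missing and 0.36 at 30%.

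**4. The favourable case.** Suppose another outcome is observed for every woman who lacks the primary one, carries the same effect of 0.35, and correlates 0.7 with the primary outcome within arm. Without arm, the estimate is then 0.319 at 20% missing and 0.306 at 30%. The shrinkage is 1 − 0.319/0.35 = 9% and 1 − 0.306/0.35 = 13%, less than half the missing fraction. Power is 0.85 against 0.88 with arm at 20% missing, and 0.78 against 0.84 at 30%.

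**5. Is the favourable case likely?** All measures are collected in an online assessment to which women are invited by e-mail. A woman who does not respond at T1 will probably lack the T1 secondary outcomes as well; this is an inference, not a statement in the article. What may remain is T2. By then controls have had access to the programme, so T2 is likely to carry less of the 3-month contrast, and the relation between T1 and T2 need not be the same in the two arms.

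**The case against.** The strongest reply is that the article never says arm is left out. Its phrase names two broad classes of data; it is not a variable list and contains no restricting word. The same sentence commits the trial to current recommendations, which cannot be consulted here and may well call for arm. The article condenses a fuller protocol, and an analysis plan could settle the exact model. All of this stands. A reader might infer that the trial has decided to impute without arm and that its primary result is therefore biased; the document does not support that. What remains is that the article did not leave imputation open. It fixed the number of imputations, the number of iterations and the basis, and that basis does not include arm.

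A reader might also infer that the effect shrinks by the full missing fraction. That holds only when nothing measured after baseline informs the missing value (steps 2 and 3). With informative post-baseline data the loss is smaller (step 4), so the missing fraction is close to an upper bound. Nor does the article say that T2 values enter the T1 imputation; the remark on T2 is a condition, not a finding of misuse.

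It could further be said that the error is conservative. That is correct: it dilutes a real effect and does not create a false one. The Discussion also concedes that power may be short if attrition is high. But that concession concerns lost information, and the section looks to imputation as the remedy. It does not cover an imputation model that itself dilutes the effect.

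Finally, the lack of a sensitivity analysis for data missing not at random might look like part of the same fault. It is not: such an analysis is commonly left to the analysis plan.

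**Conclusion.** The point holds in conditional form. The imputation basis that the article states does not include randomised arm, while the imputed data are used to test arm on all three primary endpoints. Applied as written, the plan would bias those three estimates toward no difference.

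The size depends on attrition, which the article does not give. With baseline predictors only, 0.35 becomes about 0.32, 0.28 or 0.24 at an assumed 10, 20 or 30% missing. With a strongly related post-baseline outcome observed for everyone, it becomes about 0.32 at 20% and 0.31 at 30%. The truth would probably lie between, nearer the first set if women who miss T1 miss the whole assessment. These figures assume a baseline correlation of 0.5 and data missing completely at random.

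If the team already meant to include arm, there is no bias, and only the wording needs completing. The point deserves correction before analysis because the sample size leans on the imputation and complete-data power at the target is only 0.82.

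**What to change.** Add one sentence to the analysis section or the analysis plan: missing values are imputed separately within the intervention and control arms, with the same background and outcome variables as predictors in each. This keeps the imputation consistent with the ANCOVA and lets T2 relate to T1 differently in the two arms.

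The minimum alternative is a single model with arm as a predictor. In the simulation this already restores the estimate to between 0.349 and 0.353. If T2 values are used in that model, arm-by-T2 terms should be added. The same wording should cover the per-protocol imputation.

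The cost is a line of text and one setting in the imputation software. No extra data or participants are needed, and the article shows follow-up still running when it was issued, so the change could be made before the analysis. A sensitivity analysis that shifts imputed intervention-arm values toward the control mean would be a useful extra, but it is optional and not needed to correct this point.
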